### Treatments administered

After inclusion, patients will be randomized in two arms:

Arm A: immunonutrition (ORAL IMPACT®)

Arm B: isocaloric isoprotidic nutritional support (IMPACT CONTROL) that has the same composition of ORAL IMPACT, but does not contain the immunonutriments (RNA, omega-3 fatty acids and arginine).

Oral immunonutrition (ORAL IMPACT®) and isocaloric isonitrogenous control supplement (IMPACT CONTROL) will be produced by NESTLE Nutrition, France.

In both groups, patients will be asked to drink three 74 g sachets of the product daily for 7 days before surgery. Both study product (ORAL IMPACT®) and control product (IMPACT CONTROL®) will be presented in the same form and appearance (powder) including the packaging material. The table below reports the composition of each product (Table 2).

**Table 2 Tab2:** **Composition of Oral Impact**® **and Impact Control**® **supplement (in powder form)**

Content (1 sachet)		Oral Impact® (74 g)	Impact Control® (74 g)
**Energy content**	kCal	303	303
	kJ	1275	1275
**Proteins**	g	16.8	16.8
- L-Arginine	g	3.8	0
- L-Arginine + Glutamine	g	2.46	0
**ARN**	g	0.45	0
**Nitrogen**	g	3.3	3.3
**Glucids**	g	40.2	40.2
**Lipids**	g	8.3	8.3
- Omega-3 fatty acids	g	1	0
- EPA-DHA	g	1	0
Fibres	g	3	3
Sodium	mg	320	320
Potassium	mg	402	402
Calcium	mg	240	240
Magnesium	mg	69	69
Phosphorus	mg	216	216
Chloride	mg	360	360
Iron	mg	3.6	3.6
Zinc	mg	4.5	4.5
Copper	mg	0.5	0.5
Manganese	mg	0.6	0.6
Selenium	ug	14	14
Fluoride	mg	0.51	0.51
Iodine	ug	45	45
Vitamin A	ug	300	300
Vitamin D3	ug	2	2
Vitamin E	mg	9	9
Vitamin K	ug	20	20
Vitamin B1	mg	0.36	0.36
Vitamine B6	mg	0.45	0.45
Vitamin B9	ug	60	60
Vitamin B12	ug	1.7	1.7
Vitamin C	mg	65	65
**Osmolarity**	mOsm/L	477	477

### Data collection and follow up

Patients will be followed-up for 44 days (POD30) and all data collected by investigating physician will be entered in a computerized case report forms. These recorded data are summarized in Table 3.

**Table 3 Tab3:** **Data collected during the study**

	1st consultation	D0	D7 to D12	D13	D14	D15	D16	D17	D19	D21	D24	D44
						POD1	POD2	POD3	POD5	POD7	POD10	POD30
**General data**												
First Name	x											
Last Name	x											
Sexe	x											
Date of birthday	x											
Phone number	x											
Adress	x											
Center	x											
Medical history and comorbidity	x											
Concomittant medication	x											
Preoperative chemotherapy	x											
History of liver surgery	x											
ASA score		x										
Date of 1st consultation	x											
Operating date					x							
Type of liver resection					x							
**Preoperative protein-energy malnutrition**												
Height	x											
Actual weight	x			x							x	x
BMI	x			x							x	x
Usual weight	x											
% of loss of weight in one and 6 months	x											
Albumin, prealbumin		x		x								
MNA-SF (for patients > 70 years old)	x											
Sarcopenia (Psoas area on CT scan)		x					x				x	x
**Compliance to immunonutrition treatment**												
Nutritional journal				x								
**Liver function assessment**												
PT, INR		x		x		x		x	x	x	x	x
AST, ALT		x		x		x		x	x	x	x	x
GGT, PAL		x		x		x		x	x	x	x	x
Total and direct bilirubin		x		x		x		x	x	x	x	x
Platelets		x		x		x		x	x	x	x	x
Volumetric assessment of (future) remnant liver	x						x				x	x
**Renal function assessment**												
Creatinine, urea		x		x		x		x	x	x	x	x
Sodium, potassium		x		x		x		x	x	x	x	x
Hemoglobin		x		x		x		x	x	x	x	x
White cells, lymphocytes		x		x		x		x	x	x	x	x
**Follow up**												
Overall morbidity												x
Infectious complications												x
Biliary leak												x
Length of hospital and ICU stay												x
Length of antibiotic treatment												x

Preoperative data including age, sex, medical history and comorbidities, concomitant medication, preoperative chemotherapy, history of liver surgery will be collected during the first consultation, for inclusion in the study. In addition, an evaluation of the nutritional status of the patient will be realized by collecting the following data: weight and BMI, albumin and prealbumin values, evaluation of sarcopenia on CT Scan and, for patients older than 70 years old, the MNA-SF test.

After randomization patients will receive either preoperative immunonutrition by Oral Impact® or preoperative nutritional support without immunonutriments (Impact control®) for 7 days before liver surgery. To evaluate the compliance to preoperative immunonutrition, its side effects and its impact on total food intake, patients will be asked to fill out a nutritional journal during this period.

Liver surgery will be performed by laparotomy or laparoscopy according to the decision of the surgeon.

During postoperative period, monitoring of patients will no differ from conventional monitoring after liver surgery, including daily physical examination, blood analyses at postoperative day (POD) 1, POD3, POD5, POD7 and POD10, abdominal CT scan at POD10. In addition abdominal CT scan will be done at POD2 to accurately assess the liver volume immediately after hepatectomy. Monitoring and management of postoperative complications are left to the discretion of the clinicians in charge of the patient. All complications will be collected as soon as possible, during hospitalization, and classified according to the classification of Dindo and Clavien [23].

Patients will be systematically reviewed at day 44 with abdominal CT scan to identify postoperative complications after discharge, evaluate liver regeneration and sarcopenia and to terminate their participation to the study (Figure 1).

**Figure 1 Fig1:**
[figure not shown]
**Schema depicting the workflow of the study.**

Concerning the radiological investigations performed preoperatively and then on POD2, POD10 and POD30, the assessment of remnant liver volumes and of sarcopenia, will be performed by a single radiologist.

### Randomization

Patients will be randomized in blocks, with a distribution of 1:1 for the control group and experimental group. The block size will be random and will be informed in the report of the study. Randomization will be stratified by investigator centre, type of hepatectomy and presence of an underlying hepatopathy.

The randomization list will be established using the software NQuery Advisor®v6.01, a validated system using a generator of pseudo-random numbers, so that the sequence of treatments is both repeatable and non-predictable. The physician-investigator will enter data for inclusion in computerized case report forms (eCRF), implemented using the software “Cleanweb” (Telemedicine technologies). The physician-investigator will be able then to access the randomization module of the software that will award the group in which the patient is randomized. A unique identification alphanumeric number will be assigned to each patient: “number of the center (3 characters) – Number of inclusion in the center (3 characters) - Initials of first and family names (1 and 1 characters) - randomization group”. Patients who left the study keep their number included if it has already been given. New patients will always receive a new issue of inclusion.

The randomization list will not be known in advance by the investigators. The statistical analysis and preparation of tables and graphs for the report of the study by the statistician of the study will be blinded to the extent possible. The unblinding may take place only after all data has been entered into the database of the study, all requests have been closed and the database has been frozen by the Data Manager of the study.

If necessary, unblinding may be performed according to validated procedures of the promoter. Access to randomization codes during the phase of blinding will be monitored and documented and the documentation will be kept in the “CTMS (Clinical Trial Management System)”.

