## Methods/design

### Protocol overview

The PROPILS trial is a prospective multicenter randomized placebo-controlled double-blind phase IV trial with two parallel treatment groups receiving either study product (ORAL IMPACT®) or control supplement (isocaloric isonitrogenous supplement - IMPACT CONTROL®) for 7 days before liver resection for cancer. Patients will be stratified according to the type of hepatectomy (major or minor hepatectomy), the presence of a chronic liver disease and the investigator center. The main end-point is to determine in intention-to-treat analysis, the impact of immunonutrition on the overall morbidity within 30 postoperative days. Secondary end-points will be the impact of immunonutrition on postoperative 30-day infectious and non-infectious morbidity, length of antibiotic treatment, length of hospital and ICU stay, modifications on total food intake, compliance to treatment and side-effects of immunonutrition, impact on liver regeneration and sarcopenia. At last, an ancillary study will be performed to evaluate whether the supplementary costs associated to preoperative immunonutrition could be counterbalanced by its impact in care-costs.

This study is planned for a 32-month duration with a 30-month inclusion period and is registered on clinicaltrial.gov website (NCT02041871).

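### Every patient number ends in the randomization group, so the procedure as written cannot maintain double-blinding

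*Protocol article*

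**What the plan says.** Under Protocol overview the design is stated plainly: "The PROPILS trial is a prospective multicenter randomized placebo-controlled double-blind phase IV trial". Treatments administered supports this at the level of the product, since both supplements "will be presented in the same form and appearance (powder) including the packaging material". The same section defines the arms openly, beginning "Arm A: immunonutrition (ORAL IMPACT"; Arm B is the control supplement. The sample size section uses the same two labels.

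The Randomization section describes how allocation works in practice. After entering inclusion data, the investigator can "access the randomization module of the software that will award the group in which the patient is randomized". Each patient then receives a unique number made of centre, inclusion number within the centre, and "Initials of first and family names (1 and 1 characters) - randomization group". The section also says: "The randomization list will not be known in advance by the investigators". On breaking the blind it says: "The unblinding may take place only after all data has been entered into the database of the study"; queries must also be closed and the database frozen. Unblinding is nevertheless permitted when needed, under the sponsor's procedures, and access to the codes during the blinded phase is to be monitored and documented.

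The primary endpoint is the rate of Dindo-Clavien grade II-V complications in the first 30 postoperative days (Endpoints of trial). Under Data collection and follow up the article adds: "Monitoring and management of postoperative complications are left to the discretion of the clinicians in charge of the patient".

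**The concern.** A patient number is the label by which a trial's records are found and linked. If one of its elements is the treatment group, anyone who handles the number and knows what the element means knows the allocation from the day of randomization. That is incompatible with a double-blind design, and with a rule that keeps the blind until database freeze. Monitoring access to the codes has little purpose if the code is part of the identifier.

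The endpoint makes this matter. Complications are counted by grade while their monitoring and management are left to the treating clinicians. Knowledge of the arm could therefore influence what is looked for, how it is treated and how it is graded. Antibiotic days and length of stay, both secondary endpoints, also reflect clinicians' decisions. A blind lost during the trial cannot be restored in the analysis.

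**Working it through.** **The statements side by side**

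1. Claimed: double-blind (Protocol overview; also the Abstract).
2. Stated: the investigator's module awards the group, and the patient number ends in the group (Randomization).
3. Stated: Arm A is immunonutrition and Arm B is control (Treatments administered).
4. Stated: no unblinding until data entry, query closure and database freeze (Randomization).

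On a plain reading, 2 and 3 together disclose the allocation at inclusion, which is incompatible with 1 and 4.

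The milder reading is that the group element is a masked code. With two arms and a fixed code it takes two values. Unblinding one patient then identifies the arm of every patient with the same value and, by elimination, of those with the other. Since the section permits unblinding when needed, the weakness remains. A number unique to each patient does not have it, because breaking one says nothing about the others.

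**Reproducing the plan's own figure**

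Inputs from Sample size calculation: 36% versus 24%, one-sided alpha 0.05, power 80%. With pooled variance under the null hypothesis and no continuity correction:

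n = [1.645·√(2·0.30·0.70) + 0.842·√(0.36·0.64 + 0.24·0.76)]² / 0.12² = (1.0660 + 0.5407)² / 0.0144 = 179.3, so 180 per group, as stated. The planned total of 400 gives 200 per arm.

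**Illustration of what differential recording would do**

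Assumptions, none of them from the document: no true effect, a true rate of 36% in both arms (the protocol's control rate), and recorded events in Arm A lower by d because the arm is known. With n = 200 per arm, p_B = 0.36, p_A = 0.36 − d and p̄ their mean, the chance that the planned one-sided 5% test declares benefit is

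Φ{ [d·√n − 1.645·√(2p̄(1−p̄))] / √(p_A(1−p_A) + p_B(1−p_B)) }

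| Assumed shift d | Patients in Arm A (200·d) | Argument of Φ | False-positive rate |
|---|---|---|---|
| 0 | 0 | −1.645 | 5.0% |
| 1 point | 2 | (0.1414 − 1.1131)/0.6767 = −1.436 | 7.6% |
| 2 points | 4 | (0.2828 − 1.1095)/0.6744 = −1.226 | 11.0% |
| 3 points | 6 | (0.4243 − 1.1058)/0.6719 = −1.014 | 15.5% |
| 5 points | 10 | (0.7071 − 1.0979)/0.6666 = −0.586 | 27.9% |

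With 180 per arm, the number before the drop-out allowance, the same shifts give 7.4%, 10.6%, 14.8% and 26.1%. The table shows how sensitive the test is to a few differently recorded patients. It does not estimate what will happen.

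**The case against.** The strongest reply is that the article does not say what form the group element takes or who sees it. It gives character counts for centre, inclusion number and initials but none for the group, and it does not describe the module's display. Its reference to codes with monitored access would fit a masked code held apart from users. A journal article also condenses the protocol, so the absence of a kit-numbering scheme is not itself a fault.

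This stands to the extent that one cannot conclude the trial is in fact unblinded. It does not remove the point, because the objection is to a format that the article spells out element by element, not to a missing detail. Nor do the other safeguards answer it. Identical packaging is bypassed if the number carries the group. A list unknown in advance protects concealment before allocation, not blinding afterwards.

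A reader might also infer that the radiologist, the data managers, the statistician and whoever grades complications all see the arm. The article does not support that: it does not say which identifier appears on scans or analysis files, and it names no grader. A reader might further infer that the ends of blocks become predictable. Block size is random, which reduces guessing, and visibility of past allocations is itself unproven.

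Finally, the shifts of 1 to 5 points come from nowhere in the document. That is correct, and is why they are given as a range.

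**Conclusion.** The point holds as a contradiction within the article: the identifier and allocation procedure in the Randomization section cannot maintain the double-blinding and the unblinding rule stated elsewhere. The identifier format applies to all 400 planned patients. How many allocations have been disclosed, and to whom, cannot be known from the text.

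On the plain reading the group is disclosed at inclusion. On the milder reading, which assumes a fixed two-value code, the blind depends on no patient being unblinded early. Either way the primary endpoint is exposed to bias. Its size is not derivable; the range of about 7.6% to 27.9% for a nominal 5% test rests entirely on the assumed shifts of 1 to 5 points in favour of Arm A.

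It should be corrected promptly, because the article's Study status section says data are already being collected.

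**What to change.** - Build the patient number from centre, inclusion number and initials only.
- Have the randomization module return a unique treatment number for each patient, and never a group or arm label.
- Keep the list linking treatment numbers to arms with an unblinded party outside the investigating, image-reading and analysis teams until database freeze.
- For patients already enrolled, mask the group element in all displays and exports through a documented linkage table. Record who could have seen it, and report this as a limitation.
- A comparison of the primary endpoint before and after the change may be shown, but as description only. It splits the sample and has little power to detect biased grading.
- If the group element was always a masked code, say so in the amendment and state who could see it. The change to per-patient numbers is still needed.

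The cost is an eCRF configuration change, a short amendment and some record-linkage work, which carries a risk of linkage error and so needs documented checks. No additional patients are required.

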### Statistical methods

#### Sample size calculation

The hypothesis of this phase IV trial is that immunonutrition will reduce overall postoperative 30-day morbidity rate. The sample size calculation is based on the detection of significant difference in the primary end-point parameter of the trial. We assumed a postoperative complication rate of 36% in the conventional group (Arm B) according with several studies about complication rate after liver surgery. A reduction of 33.3% would be considered to indicate the efficacy of treatment. With an expected complication rate of 24% in the immunonutrition group (Arm A), the sample size necessary for the trial with a power of 80% and a one-sided significance level of 0.05 was calculated to be 180 patients per group. An assumed 10% drop-out rate in this trial (due to non-compliance, intolerance, etc.) will raise the sample size to 198 patients per group. Therefore, at least a total of 400 patients (200×2) have to be included to the trial.

#### Statistical analyses

The statistical analysis will be based on the intention-to-treat principle with one-sided test for the primary and secondary endpoints. However, attempts will be made to analyse “per protocol”, “completer”, and “intent-to-treat” populations separately, when statistically appropriate. A p < 0.05 will be considered as significant.

First of all, an establishment of patient flow chart according with CONSORT 2010 statement [27] will be realized. This one will describe precisely the progress through the different phases of the randomized trial (enrolment, intervention, allocation, follow-up and data analysis).

Secondary, a description of demographic and clinic features of patients in the 2 groups will be calculated by using valid number, frequency count and percentage for categorical data and by using mean, standard deviation, 95%-confidence interval of the mean, minimum lower quartile, median and upper quartile for continuous data.

To study primary end-point (that is the rate of postoperative complication grading II, III, IV or V in Dindo-Clavien’s classification), Pearson Chi-square test or Fisher’s exact test will be used when appropriate.

To study secondary end-points, the Pearson Chi-square or Fisher’s exact test will be used to compare categorical variables between the 2 groups, and the independent-samples *t*-test will be used to compare continuous variables. A multivariate analysis will complete this statistical plan.

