vi)Sarcopenia: all patients will undergo 2 helical computed tomography estimations of psoas muscle area at the level of L3-L4 before surgery (day 0) then at POD30 (day 44).vii)Estimation of modifications on total food intake, compliance to immunonutrition treatment and side effects of immunonutrition. During treatment period, patients will be asked to fill in a formulary with an evaluation of food intake per day.

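### One-sided testing at 0.05 is extended to every secondary endpoint, although a direction is stated only for overall morbidity; for several endpoints, side effects included, the rejection region is undefined

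*Protocol article*

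**What the plan says.** The Statistical analyses section sets one rule for all endpoints: "The statistical analysis will be based on the intention-to-treat principle with one-sided test for the primary and secondary endpoints". The threshold follows: "A p < 0.05 will be considered as significant". No secondary endpoint is exempted. The tests named for secondary endpoints are Pearson chi-square or Fisher's exact test for categorical variables and the independent-samples t-test for continuous ones. No tail is given for any of them.

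The Endpoints of trial section lists these secondary endpoints:

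- infectious complications
- antibiotic duration
- non-infectious complications
- hospital and ICU stay
- liver regeneration
- sarcopenia
- a last item, worded as "Estimation of modifications on total food intake, compliance to immunonutrition treatment and side effects of immunonutrition"

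The Abstract and the Protocol overview also name side effects and compliance among the secondary end-points.

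A formal direction appears once, under Sample size calculation, and concerns the primary endpoint: "The hypothesis of this phase IV trial is that immunonutrition will reduce overall postoperative 30-day morbidity rate".

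**The concern.** A one-sided test needs a direction fixed in advance, and it gives up any claim in the other direction. The protocol makes that choice for the primary endpoint and then applies it to endpoints for which no direction has been set.

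The secondary endpoints fall into two groups.

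- **Benefit is the natural tail.** These are infectious and non-infectious complications, antibiotic duration and length of stay. If they follow the trial's hypothesis, an excess on the product is reported as not significant whatever its size. The non-infectious list includes liver failure, bleeding, renal failure and multiple organ dysfunction. The Background says that the product's effects in this population are unknown, so an adverse effect cannot be dismissed in advance.
- **No direction is stated.** These are side effects, food intake, compliance, liver regeneration and sarcopenia. For side effects the usual worry is an increase, which is opposite to the reduction named for morbidity. For the others, either direction is possible. With no tail fixed, the rejection region is undefined.

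What is at stake is the interpretability of the secondary and tolerance results, not the primary comparison.

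**Working it through.** **1. The plan's own figure.** Inputs from Sample size calculation: 36% in Arm B, 24% in Arm A, one-sided alpha 0.05, power 80%. Allocation is 1:1 (Randomization). The formula is the pooled-variance comparison of two proportions without continuity correction:

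n = [z(1−α)·√(2·p̄·(1−p̄)) + z(1−β)·√(p1(1−p1) + p2(1−p2))]² / (p1−p2)², with p̄ = 0.30.

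n = [1.645 × √0.42 + 0.842 × √(0.2304 + 0.1824)]² / 0.12² = 179.3, so 180 per group.

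This matches the protocol: "with a power of 80% and a one-sided significance level of 0.05 was calculated to be 180 patients per group". With 10% added it is 198, rounded up in the plan to 200 per group and 400 in total. The calculation uses the primary endpoint only, so changing the sidedness of the secondary tests does not alter it.

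**2. What the choice of tail does.** The protocol gives no side-effect rates, so the rates here are assumptions: 20% on ORAL IMPACT, 10% on control, n = 200 per arm.

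- Standard error under the null: √(2 × 0.15 × 0.85 / 200) = 0.0357
- Standard error under the alternative: √(0.20 × 0.80/200 + 0.10 × 0.90/200) = 0.0354
- Two-sided 5%: Φ[(0.10 − 1.960 × 0.0357)/0.0354] = Φ(0.85) = 0.80
- One-sided 5% toward excess: Φ[(0.10 − 1.645 × 0.0357)/0.0354] = Φ(1.17) = 0.88
- One-sided 5% toward benefit: Φ[(−0.10 − 1.645 × 0.0357)/0.0354] = Φ(−4.49) = 3.6 × 10⁻⁶. Exact binomial enumeration of the same test gives 3.9 × 10⁻⁶, about 4 in a million.

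The same calculation for two pairs of assumed rates:

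| Assumed rates (product vs control) | Two-sided 5% | One-sided toward excess | One-sided toward benefit (exact) |
|---|---|---|---|
| 20% vs 10% | 80% | 88% | 3.9 × 10⁻⁶ |
| 30% vs 20% | 64% | 75% | 3.7 × 10⁻⁵ |

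**3. One observed result under each reading.** With 40 of 200 on the product and 20 of 200 on control, z = 2.80. The one-sided p is 0.997 toward benefit and 0.0026 toward excess; the two-sided p is 0.0051. The same data are clearly significant or clearly not, depending on a choice that the protocol does not record.

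**4. Choosing the tail afterwards.** If the direction is taken from the data, the test rejects in either tail at 5%, so its true size is 0.05 + 0.05 = 0.10.

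**The case against.** The strongest objection is that the protocol never points the side-effect test toward benefit. A reader might infer that harm from the product can never be declared, however large it is. The document does not support that. The stated direction concerns overall morbidity, and a one-sided test for an excess of side effects is at least as natural a reading. Under that reading an excess would be found more easily than with a two-sided test (88% against 80% in the example). The 4-in-a-million figure holds only if a benefit tail is assumed.

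A reader might also infer that the trial cannot answer its tolerance question. That goes too far as well. The item on side effects is worded as an estimation, and rates by arm would show an excess whatever the p-value. Grade II to V complications also count in the primary endpoint, where an unfavourable rate would be visible. These points lower the severity.

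They do not remove the defect. The wording as an estimation does not exempt side effects, because the protocol names them a secondary endpoint and applies one-sided testing to all of those. The usual Pearson chi-square is non-directional, and the article does not say how it becomes one-sided, which adds to the ambiguity. The Background and Discussion suggest possible gains in infectious complications, stay and liver regeneration, but these are rationale and not stated test directions.

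Finally, the direction for each endpoint might be left to the full protocol or analysis plan. Sidedness itself is not left open, however. The article fixes it for every secondary endpoint, and a later plan with two-sided tests would contradict it.

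**Conclusion.** The point holds in limited form and should be fixed. The blanket one-sided rule has two consequences:

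- For complications, antibiotic duration and stay tested in the hypothesised direction, an excess on ORAL IMPACT cannot be called significant.
- For side effects, food intake, compliance, liver regeneration and sarcopenia, the rejection region is undefined. It could exclude harm, or it could be settled after the data are seen at a true error rate of about 10% instead of 5%.

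The first consequence assumes that those tests follow the direction given for morbidity. The power figures also rest on assumed side-effect rates and 200 analysed patients per arm; they show how much the unstated tail matters, not what the protocol specifies. The primary endpoint and its sample size are not affected.

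**What to change.** Amend the sentence in Statistical analyses so that one-sided testing applies to the primary endpoint at most. State that all secondary endpoints, side effects included, will be analysed with two-sided 5% tests and two-sided 95% confidence intervals for the between-group difference.

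The cost is one sentence. The 180 per group and 400 in total stand. The downside is somewhat lower power for secondary endpoints where only benefit was expected. The Study status section says that data are still being collected, so the change can be made and dated before unblinding.

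### One rule, one-sided p < 0.05, calls any secondary endpoint significant whatever the primary shows; with about 8 benefit-type secondaries, a false positive somewhere has a chance of about 22%

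*Protocol article*

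**What the plan says.** The article names one primary endpoint, in Endpoints of trial: the rate of complications of Dindo-Clavien grade II to V in the first 30 postoperative days. The trial is sized on that endpoint alone, "with a power of 80% and a one-sided significance level of 0.05 was calculated to be 180 patients per group".

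The significance rule in Statistical analyses is wider: "The statistical analysis will be based on the intention-to-treat principle with one-sided test for the primary and secondary endpoints". Between that sentence and the threshold, "A p < 0.05 will be considered as significant", the section also says that "attempts will be made to analyse “per protocol”, “completer”, and “intent-to-treat” populations separately, when statistically appropriate". It then names the tests for categorical and continuous secondary variables.

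Protocol overview gives the clinical secondaries: "Secondary end-points will be the impact of immunonutrition on postoperative 30-day infectious and non-infectious morbidity, length of antibiotic treatment, length of hospital and ICU stay". Endpoints of trial sets out seven numbered secondary items. Nothing in the article orders the secondary tests, makes them depend on the primary result or calls them supportive.

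**The concern.** A single threshold for all endpoints makes no distinction between the one comparison that the trial is powered for and the many that it is not. An ineffective product then has several chances to produce a result that the plan itself calls significant. Because the test is one-sided at 0.05, the bar for each is a two-sided p of 0.10.

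This matters for how the results will be read. Background and Discussion cite infectious complications, hospital stay and care costs as the gains seen in gastrointestinal surgery. The first two are secondary endpoints here. If overall morbidity shows no difference, a favourable result on infections or stay would draw attention. The printed rule would allow it to be called significant, although it could not readily be told apart from chance.

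**Working it through.** **1. Which alpha was used.** Inputs from Sample size calculation: 36% in Arm B, 24% in Arm A, power 80%, one-sided 0.05. Allocation is 1:1 (Randomization). With the pooled-variance formula:

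n = [1.645 × √(2 × 0.30 × 0.70) + 0.842 × √(0.36 × 0.64 + 0.24 × 0.76)]² / 0.12² = 179.3, which rounds up to 180 per group.

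This matches the stated 180. The two-sided version gives 228. One-sided 5% is therefore the level that was really used, and the sample-size and analysis sections agree on it.

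**2. Which secondaries to count.** The seven items in Endpoints of trial unpack to 11 variables. Three of them (food intake, compliance, side effects) are descriptive or tolerability measures and not clear claims of benefit, so they are left out. That leaves 8 benefit-type endpoints:
- infectious complications
- antibiotic days
- non-infectious complications
- hospital stay
- ICU stay
- liver regeneration at day 10 (LR10)
- liver regeneration at day 30 (LR30)
- psoas area

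The first five are the clinical ones. The medico-economic analysis and the individual complication types are not counted.

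**3. Chance of at least one false positive, all null hypotheses true.** For k independent tests it is 1 − 0.95^k:
- k = 8: 1 − 0.95⁸ = 0.337
- k = 5: 1 − 0.95⁵ = 0.226

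For k tests with a common correlation r between their normal test statistics it is

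1 − ∫ φ(x) · Φ[(1.645 − √r · x) / √(1 − r)]^k dx.

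Values from this formula (k = 5) and from a simulation of the same model with 1,000,000 draws (k = 8):

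| Assumed correlation | 8 benefit-type endpoints | 5 clinical endpoints |
|---|---|---|
| 0 | 34% | 23% |
| 0.3 | 27% | 19% |
| 0.5 | 22% | 17% |
| 0.8 | 14% | 12% |

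The article gives no correlations, so each row is an assumption. Several pairs overlap by construction (infections with antibiotic days, hospital with ICU stay, LR10 with LR30), which makes the independence row an upper figure.

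**4. Against the 5% per-test level.** At correlation 0.5 the ratios are 22/5 = 4.4 for 8 endpoints and 17/5 = 3.4 for 5. In the most favourable cell (5 endpoints, correlation 0.8) the ratio is 12/5 = 2.4.

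**The case against.** The strongest reply is that this is a condensed article. How secondaries are ordered, adjusted or labelled is commonly left to the full protocol or the SAP, so the absence of a hierarchy is not a fault. That is correct, and the point does not rest on absence. The article goes further than silence, because it states one test direction and one threshold for primary and secondary endpoints together. A later plan that made the secondaries supportive would have to override that text as well as add to it.

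A second reply is that 0.05 is only a nominal per-test level. The endpoints are labelled secondary, and the sample-size section ties efficacy to the primary rate alone. This stands in part. A reader might infer that the trial's stated 5% error is itself inflated, or that the article plans to claim success on a secondary after a failed primary. The document supports neither: the primary test keeps its 5%, no family-wise level is promised for the secondaries, and no sentence announces such a claim. The wording permits it and does nothing to prevent it.

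A reader might also be tempted to count all 11 variables (26% at correlation 0.5, 43% if independent). Three of these are not benefit claims, so those figures overstate the chance of a false benefit. Nor should the three analysis populations be treated as three equal routes to a claim. Intention-to-treat is fixed as the basis, the others are only to be attempted where appropriate, and any multiplier would need assumed correlations between populations.

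**Conclusion.** The point holds in a limited form. The article fixes a single rule, one-sided p < 0.05, for the primary and every secondary endpoint, so a secondary result is called significant regardless of the primary. If the product affects none of the 8 benefit-type secondaries, the chance of at least one such result is about 22% (14% to 34%). For the 5 clinical ones it is 17% (12% to 23%).

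These figures assume that all the null hypotheses are true and that the test statistics share a common correlation between 0.8 and 0, with 0.5 as the central value. The conclusion does not depend on the exact value, since every case considered is more than twice 5%. The primary analysis and the sample size are sound on this point. What is at stake is the standing of secondary claims.

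**What to change.** In Statistical analyses, restrict the p < 0.05 (one-sided) decision rule to the primary endpoint in the intention-to-treat population. State that all secondary endpoints, and all per-protocol and completer analyses, are supportive. They would be reported as estimates with confidence intervals and nominal p-values, without a claim of significance.

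If the sponsor wants a confirmatory secondary claim, it should pre-specify a short ordered list before unblinding. The list would be tested only if the primary is significant and would stop at the first non-significant result. Which endpoints enter the list, and in what order, is the sponsor's choice; the article does not point to a particular order.

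The cost is a few sentences. Study status says that data are still being collected, and Randomization places unblinding after the database freeze, so there is time. No patients, data or primary power are affected. The one downside is that an isolated secondary p < 0.05 could no longer be called significant when the primary fails.
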